#### Analysis strategy

Variables will be described as mean and standard deviation and percentages for quantitative and qualitative variables respectively. Comparison of quantitative variables will use Student-Fisher *T* test and analysis of variance for categorical variables and the chi-square statistical test. Standard tests (Kolmogorov-Smirnov and Shapiro-Wilks) will be used to verify the hypothesis of normal distribution of quantitative variables. If the preconditions for the application of statistical tests are fulfilled non-parametric tests will be used.

Longitudinal studies with a control group, which act in a phased manner on the caregiver-patient to see the effect on the patient, have different directions of analysis: caregiver assessment to measure acquisition of knowledge and implementation of dietary advice, and patient assessment to measure the effectiveness of educational intervention on nutritional status (MNA, diet, anthropometry, biochemistry) at 6 and 12 months in the intervention and control group and between groups.

To evaluate these effects, multivariate models of multiple linear regression and logistic regression will be created.

To measure the effect of educational intervention on the patient’s nutritional status (MNA, diet, anthropometry, biochemistry), the results will be adjusted according to degree of knowledge acquisition and implementation of dietary advice, as well as other variables that may interfere with the patient’s nutritional status such as socio-economic characteristics, caregiver education levels, and patients’ chronic diseases, dental status, degree of dependence (Barthel test), cognitive function (Pfeiffer Test), or mood (Yesavage Scale).

Initially the inclusion in the model of all variables that are part of the theoretical model will be forced, and in a second phase there will be an automatic selection by the stepwise method (backward and forward) to get reduced models.

The conditions of application of the models will be verified by standard techniques that are primarily based on analysis of the residuals.

The bilateral null hypothesis of normality, no difference and no significance of regression coefficients, will be discarded when their probability is less than 5%.

For data analysis the latest version of the software package SPSS/PC for Windows will be used.

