### Statistical analysis

#### Sample size

The main variable is the MNA score. This value has an approximate average of 25.4 and standard deviation of 3.7 points in the Spanish population [15]. It is considered that variation of 2 points is a clinically relevant value. Considering a one-sided hypothesis and admitting an alpha error of 0.05 and a power of 95%, a sample of 72 subjects in each group is needed to observe a difference of 2 points in the MNA test after educational intervention with a precision of 80%. Taking into account possible losses during follow-up, the sample expands by 20% (15 subjects) so that the study includes 87 subjects in each group, a total of approximately 200 patients.

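### The rule for choosing non-parametric tests is inverted: as written, quantitative outcomes that pass the normality check go to rank tests and those that fail stay with the t test or ANOVA

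*Protocol article*

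**What the plan says.** Three consecutive sentences in the protocol article, section Analysis strategy, set out how a test is chosen.

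1. Default tests: "Comparison of quantitative variables will use Student-Fisher *T* test and analysis of variance for categorical variables and the chi-square statistical test".
2. Check: "Standard tests (Kolmogorov-Smirnov and Shapiro-Wilks) will be used to verify the hypothesis of normal distribution of quantitative variables".
3. Consequence of the check: "If the preconditions for the application of statistical tests are fulfilled non-parametric tests will be used".

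Later in the same section comes the threshold: "The bilateral null hypothesis of normality, no difference and no significance of regression coefficients, will be discarded when their probability is less than 5" (per cent). The regression models have a separate check: "The conditions of application of the models will be verified by standard techniques that are primarily based on analysis of the residuals".

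The abstract refers only in general terms to bivariate tests and multivariate models. It does not say when a non-parametric test replaces a parametric one.

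**The concern.** A normality check placed after a parametric default has one usual purpose: to move a variable to a non-parametric test when the check fails. The third sentence attaches that move to the opposite result. It is complete and grammatical, so this is not a gap in the text. It is a working rule for selecting the test, so it is not something left to a fuller document either: the article states the rule and states it wrongly.

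Two things are at stake. First, the rule covers the simple between-group comparison of MNA, which is the key variable, and of the diet, anthropometric and biochemical measures at 6 and 12 months. Skewed measures would keep the test that the check had just called into question. Second, the wording leaves the analyst to choose between the letter of the rule and its evident intention. A prespecified rule is meant to remove that choice before the data are seen.

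**Working it through.** The plan gives no figure for this point, so there is none to reproduce. The main check is one of logic, followed by an illustration of size.

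**Logic.** Two readings are assumed. The first sentence is taken in its usual sense: t test and analysis of variance for quantitative variables, chi-square for categorical ones. The preconditions are taken to be, or to include, the normality just mentioned.

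| Result of normality check | Test under the literal rule | Test that the check is meant to lead to |
|---|---|---|
| Normality not rejected (p at or above 5%) | Non-parametric | t test or ANOVA |
| Normality rejected (p below 5%) | t test or ANOVA (default stays) | Non-parametric |

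Both rows are reversed. No other sentence in the document corrects either row.

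**Scope.**
- Bivariate comparisons of quantitative variables: affected.
- Chi-square comparisons: not affected, because the normality check applies to quantitative variables only.
- Linear and logistic regression: not affected, because their conditions are checked by residual analysis under a separate sentence.

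**Size, first row (normal outcome sent to a rank test).** Inputs from the Sample size section: SD 3.7 ("This value has an approximate average of 25.4 and standard deviation of 3.7 points in the Spanish population"), difference 2 points and 72 per group ("a sample of 72 subjects in each group is needed to observe a difference of 2 points in the MNA test"). The test level is two-sided 5%, as in Analysis strategy.

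- Asymptotic relative efficiency of the Wilcoxon–Mann–Whitney test to the t test under normality: 3/π = 0.955.
- Equivalent sample size: 72 × 0.955 = 68.8 per group.
- Approximate power of the t test at 72: 2 / (3.7 × √(2/72)) = 2 / 0.6167 = 3.243; 3.243 − 1.960 = 1.283; power 90.0%.
- Approximate power at 68.8: 2 / (3.7 × √(2/68.8)) = 2 / 0.631 = 3.169; 3.169 − 1.960 = 1.209; power 88.7%.
- Simulation, 20,000 replicates: t test 89.3%, Mann–Whitney 87.7%. With no true difference, the rejection rates were 5.1% and 5.0%.

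The loss is between one and two percentage points of power, and the type I error is kept.

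**Size, second row (skewed outcome left with the t test).** The document gives no distribution for any outcome, so this is an assumption: lognormal, SD 1 on the log scale, ratio of 1.6 between groups, 72 per group, 20,000 replicates.

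| | t test | Mann–Whitney |
|---|---|---|
| Power | 61.0% | 78.3% |
| Rejection rate with no difference | 4.5% | 4.9% |

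The loss is about 17 percentage points under this assumption (78.3 − 61.0 = 17.3), again without inflated type I error. A less skewed outcome would fall between the two cases, nearer the first as the skewness shrinks.

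**The case against.** The strongest reply is that this is an obvious slip of wording. A parametric default that is checked for normality and then dropped because normality holds makes no sense, and a competent analyst would read in the missing word. That is probably true. It limits the likely effect on results, but it does not make the rule correct, and nothing else in the document settles the matter.

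A reader might infer that every outcome is sent to the wrong test. The document does not support this: the sentence bears only on the bivariate comparisons of quantitative variables, as set out above.

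A reader might also infer that the primary result would be a rank p-value with no mean difference to set against the 2-point criterion. That does not hold either. The same section describes quantitative variables by mean and standard deviation and plans linear regression of nutritional status, with MNA named. The group coefficient from such a model is a mean difference on the MNA scale, and its standard error gives an interval. That model is adjusted for knowledge acquisition and for implementation of dietary advice, among other variables, so its estimate is not the same quantity as the unadjusted comparison. A mean difference is nevertheless available.

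Finally, it may be said that a normality pre-test should not choose the method for the primary outcome at all, and that bootstrap or robust standard errors are preferable. That criticism would apply equally to a correctly worded rule. It does not follow from the inversion and is not part of this point.

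**Conclusion.** The rule is wrong as written and should be corrected. The finding rests on the text alone and needs no assumption beyond the ordinary reading of the two neighbouring sentences.

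Its practical weight is modest. For outcomes that are close to normal, following the letter of the rule would cost very little, and the rank test would remain valid. For strongly skewed outcomes the cost could be a material loss of power, but the 17-point figure belongs to an assumed distribution and cannot be attributed to this trial. Neither example showed an inflated type I error. The remaining harm is that an operative rule contradicts its own purpose and so leaves the choice of test open.

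**What to change.** In Analysis strategy, insert the word 'not' before 'fulfilled', so that non-parametric tests are used when the preconditions fail. This changes one word and has no effect on design, data collection or sample size.

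Optionally, add a sentence saying that the between-group mean difference in MNA will be reported with a 95% confidence interval whatever the normality check shows. This keeps the bivariate result on the scale of the 2-point criterion and needs no further data.

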### Study population

Subjects will meet the following inclusion criteria: 1) participation in the Home Care program (ATDOM), 2) aged 65 years or older, 3) MNA score from 17 to 23.5 points, and 4) must have a caregiver. Exclusion criteria are: 1) MNA score outside the range of 17 to 23.5 points, 2) enteral feeding required, 3) severe dysphagia, 4) any serious illness that progresses to malnutrition, and 5) consumption of vitamin and/or dietary supplements.

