### Recruitment

Random selection of 8 PCCs of the Catalan Institute of Health (ICS) in Reus and Tarragona counties, stratified to represent different geographical areas: a) 4 PCCs in 2 cities over 100,000 population (2 in Reus and 2 in Tarragona), b) 2 PCCs in the suburbs of these cities (1 in Tarragona, 1 in Reus), c) 1 PCC in a medium-sized urban area (about 30,000 inhabitants), and d) 1 PCC in rural areas.

Subjects will be recruited by initial identification in the electronic medical record (e-cap) indicating that they meet the criteria for participation, to be verified by performing a baseline MNA test.

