### Randomization of groups

After subjects provide signed written informed consent, they will be classified randomly. From a common database, subjects will be computer-assigned to the intervention group and non-intervention (control) group in each PCC, proportionally to the total number of subjects. Subjects who choose not to participate in the study will be replaced by others of the same sex, age, and PCC to obtain the initial total sample of 97 subjects in each group.

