### Outcomes Assessment

Subject variables in the intervention and non-intervention groups: These variables will be collected at baseline and except sociodemographic variables and current medical history again at 6 months (end of intervention), and 12 months. For the intervention group there is a questionnaire on adherence to the diet.

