### Primary outcomes measures

Nutritional status variables: *Key variable:* MNA (Mini Nutritional Assessment) is a validated test with sensitivity and specificity for the diagnosis of malnutrition [12]. MNA has been selected as the main variable because it is the most used tool in PHC.

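### Effectiveness is also to be read within each arm, although patients are selected on the same baseline MNA that starts follow-up; only the between-arm difference measures the education

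*Protocol article*

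**What the plan says.** All references are to the protocol article.

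- Study population: a patient enters with an "MNA score from 17 to 23.5 points".
- Recruitment: candidates are found in the electronic record, and eligibility is "to be verified by performing a baseline MNA test". No separate screening score is described.
- Primary outcomes measures: "MNA has been selected as the main variable because it is the most used tool in PHC".
- Outcomes Assessment: "These variables will be collected at baseline and except sociodemographic variables and current medical history again at 6 months (end of intervention), and 12 months". The qualifying score is thus also the first point of the outcome series.
- Randomization of groups: "subjects will be computer-assigned to the intervention group and non-intervention (control) group in each PCC". Both arms pass the same filter.
- Intervention: controls have an initial assessment and usual home-care follow-up, but no nutritional intervention.
- Analysis strategy: one of the directions of analysis is "patient assessment to measure the effectiveness of educational intervention on nutritional status (MNA, diet, anthropometry, biochemistry"), and it is carried out "at 6 and 12 months in the intervention and control group and between groups".

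The last sentence gives one purpose, effectiveness, to the within-arm and the between-arm readings alike. It does not mark the within-arm readings as descriptive.

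**The concern.** A group chosen because one score fell inside a window tends to move towards the mean of its source population at the next measurement, with no treatment at all. Dependent older patients also change through ageing and illness. A before-after difference inside the intervention arm contains both of these together with any effect of the education, and cannot separate them. Inside the control arm there is no education to evaluate, so a reading of its effectiveness there has no meaning.

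At stake is the interpretation of the results. An improvement in the intervention arm could be presented as evidence for the education because the plan lists that reading under effectiveness. The argument does not need the drift to be large: even with no regression to the mean, a within-arm change is not a treatment effect.

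**Working it through.** The plan gives no figure for drift or retest correlation, so there is none to reproduce. The calculation below only sizes the problem.

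**Inputs**
- Window 17 to 23.5 (Study population), taken as 16.75 to 23.75 to allow for half-point scoring.
- SD 3.7, general-population mean 25.4, relevant difference 2 points and 72 evaluable patients per arm (Sample size). The 72 is used as stated.
- Home-care patients malnourished or at risk: 67.6%; home-care malnutrition: 21.3% (both Background). They come from different cited studies. I assume that both correspond to the MNA cut-offs.
- Correlation r between baseline and follow-up: assumed 0.7 to 0.9.
- Assumed normal scores, no education effect and no natural decline.

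**Formulas**, with source mean μ, source SD σ, and mean m and SD s inside the window:
- Expected drift = (1 − r)(μ − m)
- Variance of change = (1 − r)²s² + σ²(1 − r²)
- Rejection rate of a two-sided 5% paired test, n = 72: Φ(δ − 1.96) + Φ(−δ − 1.96), where δ = drift / (SD of change / √72)

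**Source mean**
- A. From 67.6% with SD 3.7 kept: μ = 23.75 − 0.4565 × 3.7 = 22.06; m = 20.72, s = 1.87.
- B. From 67.6% and 21.3% together: σ = 7 / (0.4565 + 0.7961) = 5.59; μ = 23.75 − 0.4565 × 5.59 = 21.20; m = 20.37.
- C. General population: μ = 25.4, σ = 3.7; m = 21.50.

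**Worked case (A, r = 0.7).** Drift = 0.3 × (22.06 − 20.72) = 0.40. Variance = 0.09 × 1.87² + 13.69 × 0.51 = 7.30, so the SD is 2.70. δ = 0.40 / (2.70 / √72) = 1.26. Rejection = Φ(−0.70) + Φ(−3.22) = 0.24.

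| Source | Drift at r = 0.7 / 0.8 / 0.9 | Within-arm test significant |
|---|---|---|
| A | 0.40 / 0.27 / 0.13 | 24% / 17% / 11% |
| B | 0.25 / 0.17 / 0.08 | 8% / 7% / 6% |
| C | 1.17 / 0.78 / 0.39 | 96% / 84% / 53% |

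With the window edges at exactly 17 and 23.5, A becomes 20% / 15% / 10% and B stays at 8% / 7% / 6%. At r = 0.5, with those edges, the drift is 0.60 (33% significant) for A and 0.39 (11%) for B.

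**Which source applies.** Patients come from the Home Care program. Under C only Φ((23.5 − 25.4) / 3.7) = 30% would score 23.5 or less, against the 67.6% in the Background. C therefore does not describe the population sampled.

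**Direction.** The window is bounded on both sides, with midpoint (17 + 23.5) / 2 = 20.25. A source mean of 20.25 gives zero drift, and a lower one gives apparent decline.

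**Between arms.** A simulation with no effect (4,000 runs, 72 per arm, r of 0.5, 0.7 and 0.9, all three sources) gave mean differences within 0.02 points of zero and rejection rates of about 5%.

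**The case against.** The strongest reply is that the sentence only lists where and when outcomes will be looked at. Taken literally it would measure the effect of education in patients who receive none, so a loose list is a plausible reading. The same section goes on to regression models for the intervention effect, the sample size is built on a per-group comparison, and the Discussion presents randomisation as the means of comparing the two groups. A full analysis plan, not shown here, might label within-arm results as descriptive.

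Much of this stands, and it rules out several stronger readings that a reader might infer:

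- *That a significant rise in the intervention arm, or a rise there without one in controls, counts as success under the plan.* The article names no paired test, no within-arm hypothesis and no such rule, and does not define the endpoint as change from baseline. The rejection rates above belong to a test supplied for illustration.
- *That false positives would run at 53% to 96%.* This needs the general Spanish mean of 25.4, which conflicts with the article's own home-care prevalence.
- *That the artefact must look like improvement.* Its sign depends on the source mean, and natural decline may offset or reverse it.
- *That the main comparison is biased.* It is not, because both arms are selected by the same filter and randomised.

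What the reply does not remove is the wording itself. The article states within-arm assessment as a measure of effectiveness, which is different from leaving a detail to a later document.

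**Conclusion.** The concern holds as a defect of stated inference and reporting. The protocol article assigns the measurement of effectiveness to within-arm readings as well as to the randomised contrast, and the within-arm readings cannot serve that purpose.

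On home-care inputs the artefact is about +0.1 to +0.4 MNA points, at most 0.40 / 2 = 20% of the relevant difference. A paired within-arm test would be significant in about 6% to 24% of trials instead of 5%. These figures rest on an assumed correlation of 0.7 to 0.9, normal scores, no natural decline, and a source mean back-calculated from the Background prevalences. The objection to within-arm effectiveness claims rests on none of them. The trial's main contrast is sound on this point.

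**What to change.** In Analysis strategy, state that the effect on MNA, diet, anthropometry and biochemistry is judged only on the randomised between-group difference at 6 and 12 months. Report within-arm means and changes descriptively, without p-values or claims of effectiveness.

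This is a change of wording: no added patients, visits or data. The cost is the loss of within-arm significance statements, which are not valid evidence for the education.

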### Caregiver variables in the intervention and non-intervention groups

These variables will be collected at baseline for both groups, except for the assessment of knowledge acquisition, which will be collected in the intervention group before the intervention, immediately after, and at 1–6–12 months thereafter.

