##### Knowledge acquisition

An 11-item questionnaire on basic concepts explained in the nutritional education intervention, designed by researchers.

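### The model for the intervention effect adjusts for caregiver knowledge and uptake of dietary advice, which are consequences of the education; knowledge is recorded in the intervention arm only

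*Protocol article*

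**What the plan says.** The Analysis strategy section of the protocol article states the purpose of the model and its adjustment set in one sentence. The purpose is "To measure the effect of educational intervention on the patient’s nutritional status (MNA, diet, anthropometry, biochemistry" and so on. The adjustment is that "the results will be adjusted according to degree of knowledge acquisition and implementation of dietary advice", followed by ordinary covariates such as chronic disease, dental status and dependency. On model building it adds: "Initially the inclusion in the model of all variables that are part of the theoretical model will be forced". Stepwise selection comes second.

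Other sections show what the two variables are and who provides them:

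- Knowledge acquisition: "An 11-item questionnaire on basic concepts explained in the nutritional education intervention".
- Caregiver variables: these are collected at baseline in both groups, except knowledge, "which will be collected in the intervention group before the intervention, immediately after, and at 1–6–12 months thereafter".
- Outcomes Assessment: "For the intervention group there is a questionnaire on adherence to the diet".
- Intervention: controls receive no nutritional intervention.

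The Analysis strategy also describes designs of this kind as ones "which act in a phased manner on the caregiver-patient to see the effect on the patient". It mentions Student t tests for quantitative variables and an assessment of nutritional status at 6 and 12 months within and between groups.

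**The concern.** A randomised comparison estimates the effect of being allocated to education. Adjusting it for variables that the education itself changes turns it into something else: at best a direct effect that leaves out the intended pathway, and one no longer protected by randomisation. By the protocol's own account, knowledge of the taught content and use of the advice are that pathway.

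There is also a plain data problem. A covariate with no values in one arm cannot serve in a between-arm regression. Anyone who follows the sentence must either lose the control arm or invent control values. At stake is the adjusted estimate for MNA, the key variable, and for diet, anthropometry and biochemistry.

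**Working it through.** The plan gives no figure for this adjustment, so there is none to reproduce. For scale I take three inputs from the Sample size section: a difference of 2 MNA points, SD 3.7 and 72 per group. (The stated one-sided 5% and 95% power give 2 x [3.7 x (1.645 + 1.645) / 2]^2 = 74.08, so 75 rather than 72. That is a separate matter and does not affect this point.)

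**Unadjusted benchmark.** SE = 3.7 x sqrt(2/72) = 0.62. Power for 2 points at two-sided 5% is about 90%.

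The protocol does not say how missing control values of knowledge would be handled, so I take both obvious routes.

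**(a) Complete cases.** All control records lack knowledge. Of 144 patients, the 72 in the intervention arm remain. The design matrix has three columns (intercept, arm, knowledge). Arm is now constant and equal to the intercept, so the rank is 2 and the arm coefficient is not estimable. This step needs no numerical assumption.

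**(b) Controls coded 0.** Assume an intervention-arm score with mean 8 and SD 1.5 out of 11; the protocol gives neither.

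- Between-arm variance of the score: 8^2/4 = 16. Pooled within-arm variance: 1.5^2/2 = 1.125.
- R^2 of the score with arm: 16/(16 + 1.125) = 0.934. VIF = 1/(1 - 0.934) = 15.2 before rounding.
- SE of the arm coefficient: 0.62 x sqrt(15.2), about 2.4. Simulation (4,000 runs) gave 2.44.
- Expected arm coefficient: 2 - 8 x slope, where slope is MNA points per knowledge point within the intervention arm.

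| Assumed slope | 2 - 8 x slope | Simulated mean | Rejection rate |
|---|---|---|---|
| 0 | 2.0 | 2.03 | 13% |
| 0.3 | -0.4 | -0.47 | 5% |
| 0.8 | -4.4 | -4.40 | 43%, with a negative mean estimate |

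The true effect of allocation is 2 points in every row. The coefficient is the arm difference extrapolated to a knowledge score of 0.

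**(c) Knowledge measured in both arms.** This is not what the protocol plans, but it separates the mediator problem from the missing-data problem. Assume the education shifts the mediator by 1 SD. The adjusted coefficient is 2 x (1 - mediated share).

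| Mediated share (assumed) | Adjusted coefficient | Power, adjusted | Power, unadjusted |
|---|---|---|---|
| 0% | 2.0 | 82% | 90% |
| 25% | 1.5 | 58% | 90% |
| 50% | 1.0 | 33% | 90% |
| 75% | 0.5 | 12% | 89% |
| 100% | 0.0 | 6% | 89% |

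The unadjusted coefficient stays at about 2.0 throughout.

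**The case against.** The strongest reply is that the randomised comparison survives. The Analysis strategy plans t tests and a between-group assessment, and the Abstract lists bivariate tests beside the multivariate models. That stands. A reader might infer that the trial can no longer estimate its effect, or that the effect is bound to vanish. The documents support neither. The unadjusted comparison is untouched, and an estimate of 0.0 in (c) needs full mediation, which is only an assumption. Monthly home monitoring and individualised advice could act without raising an 11-item score. But the protocol does not name the unadjusted comparison as primary, and its sentence on measuring the effect specifies the adjusted model.

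Second, the intervention-only questionnaire concerns adherence to the diet, whereas the model uses implementation of dietary advice. That these are the same measure is an inference. It is plausible, because no other measure is described and controls get no study advice. If implementation were instead taken from the food frequency questionnaire, controls would have values. It would still be post-randomisation, and diet is itself an outcome of the model. For knowledge the restriction to one arm is explicit.

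Third, the sentence might be meant as a mediation or within-arm analysis. The section does treat caregiver knowledge and uptake as a separate direction of analysis, which helps the fix. But it then lists both again as adjusters in the effectiveness model and does not restrict that model to one arm. A mediation analysis would need knowledge measured in controls.

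Fourth, a reader might add that Barthel, Pfeiffer and Yesavage are repeated at 6 and 12 months and could also enter as post-randomisation values. The text does not say that follow-up values will be used. It presents them as ordinary covariates, and their timing is a detail that an article may leave to the full plan. I do not count it as an error.

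**Conclusion.** Wrong as written, for the adjusted effectiveness model. That both adjusters are consequences of the education, and that knowledge has no control values, follows from the protocol itself. So does the failure of the complete-case model.

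The size under any other handling rests on assumptions. With zero coding, the roughly fourfold rise in standard error depends on the assumed mean and SD, and the coefficient depends on an unknown slope. With measurement in both arms, the loss runs from none to all of the 2 points according to the mediated share. The accurate description is therefore inestimable, distorted or attenuated, depending on handling. The defect lies in one of the two planned comparisons, but it is the one that the protocol assigns to measuring the effect.

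**What to change.** In the Analysis strategy, delete knowledge acquisition and implementation of dietary advice from the adjustment set of the effectiveness model. State that the effect is estimated by randomised arm, with only covariates recorded before randomisation, and say which comparison is primary. The pre-intervention knowledge score cannot serve as a covariate either, because controls do not provide one.

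Report knowledge and adherence separately, as process or dose-response analyses within the intervention arm, labelled non-randomised. The change is to wording only and needs no new data. A formal mediation analysis would be a different undertaking, because both variables would then have to be measured in controls too.
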